### *Qualitative Data*

Qualitative data on intervention acceptability in the context of women's ART initiation and follow-up will be used to address objective 2.5.E. The in-depth interview transcripts will be reviewed to develop a set of themes emerging from the interviews, with open-coding using HyperRESEARCH 2.8.3. (ResearchWare, Inc. 2009, <http://www.researchware.com/>) to allow new themes to emerge over time. In this way, the initial codes will be revised and refined to create a code-book to help guide further analysis. This codebook will be developed after 5-6 interviews are completed, and the codebook revisited after the full cohort of interviews has been transcribed. Thematic analysis will focus on dominant themes relayed by interview subjects, as well as the context in which themes emerged. Participant observation will be similarly coded with the same themes as in-depth interviews.

The qualitative analysis will draw on corresponding participant data from the quantitative arm of the study, and make use of this information to strengthen the analysis. At two points in the recruitment process, qualitative and quantitative participants will be compared according to key demographic indicators and adjusted accordingly to roughly resemble the quantitative arm.

### Cost-effectiveness

Cost-effectiveness analysis (objective 2.5.F) will be analyzed from the health systems perspective. Costs will be defined as the mean cost per woman from the start of ANC through different points in time (eg, 6 or 12 months postpartum). Calculations will follow standard methods, with costs as quantities of resources utilized multiplied by unit costs. Resources include health services visits, laboratory investigations, and antiretroviral costs as well as the program-level costs (eg, patient education and adherence support materials) for each study group. Unit costs will be defined as the full economic cost for each item. Human resource costs will be calculated separately to enable an estimation of the number of different cadres of staff needed to provide services in each study group at different levels of scale. Outcome data will be used to calculate the incremental cost required to improve patient outcomes. Costs and outcomes will be discounted appropriately.

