These two arms both employ standard provincial protocols for ART services (with identical medications and routine monitoring); they differ by the length of time women remain in the MCH-focused ART service at the Gugulethu MOU before they are referred to general ART clinics.

All women participating in Phase 3 will be followed through 18 months postpartum. The total length of participation in the study will vary based on gestational age at enrolment into Phase 2, ranging from a minimum of approximately 52 weeks to a maximum of approximately 80 weeks. Study measures will be taken at measurement visits that are conducted away from routine antenatal, postnatal or ART services (separate research staff working in a separate location). Measurements include questionnaires and HIV viral loads at each visit, as well as abstraction of clinical data on routine antenatal, postnatal and ART services received, for both mothers and infants.

Each Phase of the study has a separate Informed Consent (IC) process outlining the purpose and process of that Phase of the study, the risks and benefits of participation, the alternatives to participation, and that the decision to participate will in no way affect the medical care they receive. Participants may withdraw from the study at any time. Participants will receive up to R100 reimbursement to compensate for transport and time involved in attending the visit. They will be given R80 in grocery vouchers and R20 cash to cover transport for each visit. At the birth visit and the final study visit (at 18 months postpartum) they will also receive a small gift up to the value of R50 (eg, baby clothes or nappies).

Given the importance of MTCT in ART-eligible women, and the increasing importance of the postpartum period as a time of MTCT risk when breastfeeding, the proposed study has the potential to make a significant contribution to services that maximize the benefits of antiretroviral therapy for both maternal and child health.

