### **Secondary objectives**

- 2.1 To characterize the health status of the population of HIV+ pregnant women seeking antenatal care at the Gugulethu Midwife Obstetric Unit (MOU) including maternal and infant outcomes
- 2.2 To describe uptake and timing of services received throughout the PMTCT cascade, including antenatal ART initiation and follow-up, at the Gugulethu MOU
- 2.3 To examine whether there is variation in the impact of the two postpartum HIV care strategies on the primary outcome between subgroups of women according to their demographic, clinical and psychosocial characteristics, measured antenatally and postnatally.
- 2.4 To describe changes in women's clinical and/or psychosocial characteristics between the antenatal and postnatal periods, and investigate how these are independently associated with the primary outcome
- 2.5 To compare MCH-focused ART services to general adult ART services on:
  - a. Women's missed visits and loss to follow-up on ART up to 18 months postpartum
  - b. Breastfeeding practices, including duration of exclusive feeding and weaning patterns
  - c. Maternal viral suppression throughout the breastfeeding period as well as before and after cessation of breastfeeding
  - d. Infant health outcomes including growth parameters and incidence of respiratory and/or diarrhoeal illness
  - e. Rates of HIV transmission from mother-to-child at 6 weeks and 12 months postpartum
  - f. Acceptability of different strategies for delivering HIV care and treatment during the postpartum period
  - g. Cost-effectiveness in delivering HIV care and treatment during the postpartum period
  - h. Developmental scores of 1 year old infants

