**Phase 3** of the study is a randomised trial of strategies for delivering ART to women during the postpartum period (objective 1) with measurement of secondary outcomes during the postnatal period (objectives 2.3, 2.4, 2.5 and 2.6). Women enrolled in Phase 2 who are breastfeeding their infants will be approached to participate in the trial at the routine postpartum clinic visit (this takes place within 7 days of birth and is the only standard postpartum care for women). This coincides with the final Phase 2 study visit. Informed Consent #3 will be completed after completion of the Phase 2 postpartum visit. Randomization will take place after completion of Informed Consent #3.

Randomization will be to one of two approaches to providing ART during the postpartum period to HIV-infected mothers who are breastfeeding:

- **Arm A:** referral to general adult ART services from approximately 4-8 weeks postpartum (the local standard of care)
- **Arm B:** receipt of ART in the antenatal clinic, as part of a MCH-focused ART service that only refers women to general adult ART services after the end of breastfeeding and once infants' final HIV status is determined

Women randomized to Arm A or Arm B will be asked to return for five additional study visits during the postpartum period at approximately 6 weeks, 3 months, 6 months, 9 months, 12 months and 18 months postpartum. Details of study measurement visits conducted in both the antenatal and postnatal periods are described below in Section 8.

After completion of the 12 months postpartum visit, women will be invited to participate in an additional infant neurodevelopmental assessment. This assessment is described in more detail in Section 8.

For women enrolled in Phases 1 and 2 of the study, participation will not impact on any aspect of routine antenatal and obstetric care during pregnancy. Similarly, throughout the antenatal period women's HIV-related care (including PMTCT services and ART) will not be affected in any way by participation, with ART initiated according to the current standard of care. For women enrolled in Phase 3 of the study, participation will only impact on the setting and approach to providing ART services to mothers during the postpartum period, comparing immediate referral to general adult ART services versus ongoing care in MCH-focused ART services within the Gugulethu MOU.

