#### *Phase 3: Subset of Phase 2 participants eligible for randomization*

- Consented and participated in Phase 2
- Initiated ART during the antenatal period
- Currently breastfeeding within <7 days postpartum (with an allowable window of up to 28 days postpartum)
- Willingness to be randomized and return for postnatal study visits
- Able to provide informed consent for research (Informed Consent #3)

*Infant neurodevelopmental assessment: Infants of women completing the 12 months postpartum visit*

- Completed participation in Phase 3
- Infant does not have any major congenital anomaly
- Infant is not known to be HIV infected at age 12 months

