### *Randomization*

Randomization will take place at the end of the study measurement visit within the first week postpartum. Randomization will follow a dynamic permuted block design. Randomization numbers will be generated prior to the start of the study, and placed in sequentially numbered opaque envelopes. Randomization envelopes will be stored in a locked cabinet in the study office at UCT that will be accessed by the study coordinator when a woman is fully consented and has completed the immediate postpartum study visit, with independent documentation of the participant ID number, randomization date, and randomization assignment. The study coordinator will provide the MOU-ART service with a regularly updated list of women to be retained within the MOU-ART service until they have ended breastfeeding. The study coordinator involved in randomization will not be involved in interviewing participants.

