### Cost-effectiveness

Costing data will be used alongside findings on clinical outcomes in order to understand the cost-effectiveness of the two strategies for ART services during the postpartum period. Data on unit costs, including human resources costs, will be abstracted from routine facility accounts, facility utilization data and staffing plans, and pharmacy accounts maintained by the PGWC; data on service utilization by participants will come directly from the study data; program costs will be based on local standards for training and materials development; overhead costs will be based on PGWC accounts.

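### Costs for the arm comparison start at antenatal care, before randomisation, which costs precision in the incremental cost without biasing it

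*Protocol*

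**What the plan says.** The Cost-effectiveness paragraph of Section 10 defines the cost measure: "Costs will be defined as the mean cost per woman from the start of ANC through different points in time", with 6 and 12 months postpartum given as examples of end points. It then uses costs and outcomes by study group to derive an incremental cost for improved outcomes, from a health systems perspective.

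The question is framed more narrowly elsewhere. Secondary objective 2.5.g in Section 2 reads "Cost-effectiveness in delivering HIV care and treatment during the postpartum period". (Section 10 labels it 2.5.F, but item f in the list is acceptability.) The Cost-effectiveness paragraph of Section 8 likewise refers to "the cost-effectiveness of the two strategies for ART services during the postpartum period".

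Allocation comes after delivery. Section 8, Randomization, says "Randomization will take place at the end of the study measurement visit within the first week postpartum", and the Phase 3 inclusion criteria in Section 4 allow a window of up to 28 days after birth. On antenatal HIV care, the Overview in Section 3 says that it "will not be affected in any way by participation, with ART initiated according to the current standard of care".

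Nowhere does the protocol say that antenatal cost will be subtracted, reported apart from postpartum cost, or used as a covariate in the arm comparison.

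**The concern.** A cost incurred before randomisation carries no information about the effect of the randomised strategy. Antenatal visits, tests and drugs are the same standard of care for every woman, but their quantity differs between women. Section 6 describes women on ART at the obstetric unit returning every 1 to 2 months until delivery, so a woman who books early accrues more visits and refills than one who books late. The synopsis notes that "The total length of participation in the study will vary based on gestational age at enrolment into Phase 2".

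Putting this component into each arm's mean cost adds between-woman variation to the incremental cost, which is the numerator of any cost-effectiveness ratio. At stake is the width of the uncertainty around the result for one secondary economic objective.

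**Working it through.** **Inputs from the protocol.** The cost window opens at the start of antenatal care (Section 10). Randomisation is after delivery (Section 8). Antenatal HIV care is unaffected by participation (Section 3). Allocation is 1:1 with about 195 women per arm (Section 10, Sample size considerations). The cost paragraphs state no numerical result, so there is no figure of the plan's own to reproduce.

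**Inputs assumed.** The protocol gives no cost, cost SD or correlation. Let A be antenatal cost and P post-randomisation cost, r = SD(A)/SD(P), and ρ = corr(A, P). I take r = 0.25, 0.5 and 1, and ρ = 0 and 0.3.

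**Step 1: expectation.** By randomisation, the expected arm difference in A is 0. So E[difference in (A + P)] = E[difference in P], and the target is the same under either start date.

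**Step 2: variance.** With equal arms and a common covariance structure, relative to counting P alone:

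Var[diff(A + P)] / Var[diff(P)] = 1 + r² + 2ρr

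The SE factor is the square root.

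| r | ρ | 1 + r² + 2ρr | SE factor |
|---|---|---|---|
| 0.25 | 0 | 1 + 0.0625 + 0 = 1.0625 | 1.03 |
| 0.5 | 0 | 1 + 0.25 + 0 = 1.25 | 1.12 |
| 1 | 0 | 1 + 1 + 0 = 2.00 | 1.41 |
| 0.25 | 0.3 | 1 + 0.0625 + 0.15 = 1.2125 | 1.10 |
| 0.5 | 0.3 | 1 + 0.25 + 0.30 = 1.55 | 1.24 |
| 1 | 0.3 | 1 + 1 + 0.60 = 2.60 | 1.61 |

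In sample-size terms, at r = 0.5 and ρ = 0, 195 women per arm give the precision of 195/1.25 = 156 per arm.

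**Step 3: when there is no loss.** The ratio is below 1 only if r² + 2ρr < 0, that is ρ < −r/2. At r = 0.5 this needs ρ below −0.25. The protocol gives no reason to expect a clearly negative correlation.

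**Step 4: the same effect seen as imbalance.** The chance difference in mean antenatal cost has SE sqrt(2/195) = 0.10 antenatal SDs. This is what produces the widening in Step 2. It is not a further loss on top of it.

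**Step 5: covariate adjustment.** Regressing A + P on arm and A gives exactly the same arm coefficient and SE as regressing P on arm and A; only the slope on A shifts, by 1. Relative to an unadjusted comparison of P, adjustment multiplies the variance by about 1 − ρ², which is 0.91 at ρ = 0.3.

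**The case against.** The strongest reply is that Step 5 makes the start date irrelevant once the contrast is adjusted for antenatal cost, and that the choice of estimator is commonly left to an analysis plan or health-economic plan not seen here. Section 10 says only that calculations follow standard methods. It names no estimator or interval. This shows that the loss is avoidable, but the plan does not state the adjustment. What it does fix is the cost window, and that window does not fit the question.

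A second reply is that whole-pathway cost is useful. The synopsis and Section 1 call for attention to the complete PMTCT cascade, and the same unit delivers both antenatal and early postpartum ART. That stands as a reason to report the figure, but not to use it as the arm contrast.

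A third reply concerns size. Antenatal care follows one standard pathway at one clinic. Postpartum cost runs for up to 12 months across several facilities, with drop-out and re-referral. Equal SDs (r = 1) would then be extreme, and at r = 0.25 and ρ = 0 the loss is only 3%. This also stands.

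A reader might infer more than the protocol supports. One inference is that the incremental cost is biased or no longer describes the postpartum strategies. It is not biased, because antenatal cost cancels in expectation and only each arm's absolute mean cost changes. Another is that chance imbalance is a second harm beside the added variance. They are one effect.

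**Conclusion.** The point holds as a matter of precision and clarity. The protocol defines costs for an arm comparison over a window that opens before randomisation, while its stated question is postpartum. The expected incremental cost is unchanged. Without adjustment, its SE is multiplied by 1.03 to 1.41 at ρ = 0 and by 1.10 to 1.61 at ρ = 0.3, for r from 0.25 to 1. These ranges rest wholly on assumed values of r and ρ, so the 41% and 61% figures should not be read as expected losses. The direction is secure unless antenatal and postpartum costs are negatively correlated to the extent of ρ ≤ −r/2. Severity is low.

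**What to change.** Amend the Cost-effectiveness paragraph of Section 10 in one of two ways for the arm comparison: count costs from randomisation to the horizons already named (for example 6 or 12 months postpartum), or keep the window and adjust the incremental cost for antenatal cost as a baseline covariate. In either case, report mean cost per woman from the start of antenatal care separately, labelled as a description of the whole pathway.

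The same cost data serve, so no new collection is needed. The price is about a sentence of text and one extra reported figure. If costs run from randomisation to a fixed postpartum age, the wording should acknowledge that the start can fall up to 28 days after birth, so the length of the window varies slightly between women.

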## **11. Ethical considerations**

### Ethical review

The study protocol, informed consent forms, all data collection tools, and other requested documents will be reviewed and approved by the Columbia University Medical Center Institutional Review Board (CUMC-IRB) and the University of Cape Town Faculty of Health Services Research Ethics Committee (UCT-REC). Subsequent to the initial review and approval, the CUMC-IRB and UCT-REC will review progress of the study at least annually.

### Informed consent

Informed consent before enrolment into Phase 1, 2, or 3 will be delivered in participants' home language (isiXhosa) by trained interviewers following a standardized script. This script details the purpose of the study, the nature of randomization, study procedures throughout the antenatal and postnatal periods, and the risks and benefits to mothers and infants that participants may encounter during the study. Here and throughout the study, study staff will emphasize to participants that:

- Participation is entirely voluntary, and their choice regarding participation will in no way influence the quality of antenatal or postnatal routine medical care for mothers or their infants
- Women may exit the study at any time for any reason without compromising the quality of health care received.

Note that separate informed consent documents will be used in this study:

1. Informed Consent #1: This consent will be completed by all HIV-infected pregnant women making their first antenatal visit who meet eligibility criteria for inclusion in Phase 1 (up to 1000 women during the 12 month recruitment period). This consent form provides details of the overall purpose of the study and outlines the following study procedures: (1) completion of an enrolment questionnaire (including demographic and behavioural questions); (2) blood draw, and; (3) permission to conduct chart review and data abstraction from routine clinical records through pregnancy and post-partum period; (4) permission to contact participant regarding future research.
2. Informed Consent #2: This consent will be completed by a subset of women from Phase 1 who are deemed ART-eligible and who meet eligibility criteria for inclusion in Phase 2. This consent form introduces the overall purpose and process of the remainder of the study (Phase 2/3) and the specific procedures for Phase 2 antenatal/postnatal measurement visits (through 1 week postpartum).
3. Informed Consent #3: This consent will be completed by a subset of women from Phase 2 who initiated ART during the antenatal period, who are breastfeeding their infants, and who meet other eligibility criteria for inclusion in Phase 3. This consent form details the overall purpose of the study, the two study arms, the concept and process of randomization, and the procedures for Phase 3 postnatal measurement visits (through 18 months postpartum).
4. Informed Consent for Infant Neurodevelopmental Assessment: This consent will be completed by Phase 3 participants who complete the 12 months postpartum visit and who have infants who are HIV-uninfected and meet other eligibility criteria for participation in this additional assessment. This consent form details the overall purpose of the assessment and the procedures for conducting the developmental assessment.

English versions of the informed consent documents are provided in the Appendix to this document. Translated isiXhosa versions (as well as a certification of their translation and back-translation) will be lodged with the IRB/REC before the start of the study.

## Risks

The potential risks to participants in the study include:

- Risks associated with collection of biologic specimens, through complications of phlebotomy.
- Risks associated with collection of self-reported behavioural and psychosocial information, related to psychosocial distress raised by questionnaire items involving social support, mental health, or disclosure of HIV status or ART use.
- Risks due to loss of confidentiality due to study procedures—for instance, in the process of data collection or participant follow-up.

All participants will be informed of these risks, and the strategies to minimize these, as part of the informed consent process. The alternative to participation is the referred initiation strategy, and each of these classes of risk are encountered during routine health care services. However, the study team has integrated planned specific steps in study design and conduct to minimize the possibility of these risks. These steps draw directly from prior experiences conducting research on HIV prevention and treatment in Gugulethu and similar communities across Cape Town.

## Benefits

### *Direct benefit*

The major potential direct benefit from participating in this study is optimized ART use during pregnancy and postpartum. This, in turn, is likely to minimize the risk of mother-to-child HIV transmission while maximizing maternal health (recognizing that optimizing the health of an HIV-infected mother has benefits both for her and her children, whether HIV infected, HIV-exposed, or HIV-uninfected). Given the high risk of MTCT and high risk of morbidity and mortality in ART eligible pregnant women, these benefits substantially outweigh any risks associated with participation in the study.

### *Indirect benefit*

By identifying the optimal strategy for delivering ART to women during the postpartum period, this study has the potential to lead to improved ART services for HIV-infected women in Cape Town, the Western Cape Province, and across South Africa. To this end, the involvement of provincial policy makers involved in HIV care and treatment and maternal and child health will help maximize the indirect benefits of the study through strengthened public sector health care services for HIV-infected pregnant women.

